### Interventions for control and intervention groups

We will provide the participants in both experimental groups with an app-based parenting education program that targets training on pediatric diseases and parenting skills but excludes information about unintentional injury prevention. The education program will use short essays, games, cartoons and videos to disseminate knowledge and skills about optimal parenting of young children. The content, interaction, survey and feedback, and personal module of app will be identical for both groups.

The intervention group’s app will have additional components that are focused on unintentional injury prevention. As detailed below, the intervention group’s app will have features geared particularly toward parenting and education on child injury prevention, including some features that rotate seasonally (e.g., drowning prevention in summer).

Both parenting and injury prevention features in the app will be available throughout the intervention time period so that the users can retrieve any information they want on a repeated basis.

### Intervention design

The intervention was developed based on the Theory of Planned Behavior [28], the Haddon Matrix [29], the Mobile Learning framework [30], and a needs assessment that consists of focus groups and online surveys among key stakeholders (including local caregivers of preschoolers and preschool teachers).

This intervention comprises four active modules: (a) content learning, (b) interaction, (c) survey and feedback, and (d) personal modules.Content learning: Content learning includes lessons to teach caregivers basic knowledge concerning prevention of ten common causes of unintentional injuries: exposure to animate mechanical forces (including animal bites and being trampled or bumped into by another person); exposure to inanimate mechanical forces (including pinched, cut or punctured by lifts and other objects); falls (including falls from heights); contact with heat and hot substances; exposure to smoke, fire and flames; transport accidents; accidental threats to breathing; unintentional poisoning by and exposure to noxious substances; unintentional drowning and submersion; and exposure to electric currents.

We will convey empirically-supported injury prevention knowledge to caregivers using strategies developed through focus groups among caregivers, discussion among content experts, and pilot testing. The needs assessment will guide decisions concerning the modes of training (e.g., through short written statements with pictures, cartoon vignettes, video testimonials, interactive games) and the length of each aspect of knowledge disseminations (expected to be somewhere in the 2–5 min range).

Parents will access knowledge-based learning through the “recommended knowledge” module on the app’s homepage (Fig. 3a, the app homepage was translated into English appears in Additional file 2) and will be reminded about unread knowledge module components through notifications that pop up on the smartphone screen when participants turn on the app (Fig. 3b). Further, caregivers will have the option to bookmark knowledge dissemination components by clicking a star on the bottom right corner of their screen (Fig. 3c), permitting access from their homepage to read/view knowledge components at convenient times. When participants fail to use the app for more than 1 month, an alert will be sent via text-message to their smartphones. To avoid contamination between participants in the intervention and control groups, all app-based programming will be restricted for use to assigned accounts for each participant, with sharing features disabled between participants (and between the participants with non-participants) throughout the study period.b.Interaction: Three modules will be created to facilitate communication between users (study participants) and between users and injury prevention experts: the forum module, the expert consultation module, and the user comments module. The forum module (Fig. 3d) will allow users to read and discuss specific topics with each other. Two forum topics will be released each week, one for parenting skills outside injury prevention (released to both intervention and control group) and the other focused specifically on unintentional injury prevention (intervention group only). A week later, discussion records will be reviewed by an expert in injury prevention and parenting, who will answer questions presented on each topic and provide expertise on the matter.

**Fig. 3 Fig3:**
[figure not shown]
Homepage of app intervention. Note: The app homepage was translated into English appears in Additional file 2. Eight images within the figure were derived from the app “Baohusan” that has been developed by the research team for unintentional injury prevention among preschool students and will be tested in this trial

The online expert consultation module (Fig. 3e) will be organized to focus on a particular topic related to injury prevention for the intervention group each month. In it, caregivers will ask experts questions through online chatting and the expert will provide private and individualized responses.

Finally, users may provide comments below each knowledge dissemination to offer another method for caregivers to communicate with each other.c.Survey and feedback: The questionnaire module (Fig. 3f) will support online data collection. The module will incorporate several strategies to encourage questionnaire completion. If an online questionnaire is not completed, a reminder notice will appear on the scroll screen when the user turns on the app. Further, automated text messages will be delivered to users 1 week before completion deadlines.

Customer service agents will be available daily (7.5 h on weekdays and 6 h on weekends, except for national holidays), using app-based online chatting to support users and help them solve any technical problems on use of the app. Outside of working hours, users will be able to access FAQs (Frequently Asked Questions) through an automated response system (Fig. 3g).d.Personal modules: Research suggests health education compliance and health behavior change is more likely if users can engage personally and feel “connected” to the program [31]. Thus, we will allow participants to select the color of the interface in their app according to their preferences (e.g., pink, yellow, blue) (Fig. 3h).

### Approaches to increase compliance to the intervention

Four approaches will be implemented to encourage participation and increase compliance with using the app. First, participants will be awarded virtual currency during use, which can be exchanged for incentives such as wireless internet fees for smartphone and data use. Second, participants who complete log-ins for 7 days, as recommended, will be entered into a lottery to win additional virtual currency prizes. Third, coordinating teachers at each preschool will remind participants to use the app through multiple school-family communication platforms weekly (e.g., social media platforms). Finally, we will offer monthly awards to the three students in each classroom whose caregivers use the app with the greatest frequency with a small gift (about 5 Chinese Yuan).

### Feasibility testing

Prior to the formal experiment**,** 20 caregivers of preschoolers will be recruited for feasibility testing, 10 in the intervention group and 10 in the control group. Following a two-week pilot testing period, participants will be asked to complete an online usability/feasibility questionnaire that addresses their evaluations of the contents, readability, app functions, app interfaces and operability of the app. The results of testing will guide refinement of the app and survey questionnaires prior to the full study.

### Primary outcome measure

The primary outcome measure will be the incidence of unintentional injury among preschoolers in the prior 3 months, as collected both at 3-month and 6-month follow-up visits. Following previous epidemiological studies [32], we define an injury event as one that meets any of the following criteria: (i) child receives medical treatment by a doctor or other medical professional following an injury; (ii) child receives first aid by a family member, teacher or other non-medical staff following an injury (e.g. takes medication, receives massage or hot compress); and/or (iii) child is restricted from school or other activities, or is kept in bed/rest for more than a half-day following an injury.

Our primary outcome variable will be unintentional injury incidence, calculated as$$ \frac{\mathrm{Number}\ \mathrm{of}\ \mathrm{preschoolers}\ \mathrm{experiencing}\ \mathrm{an}\ \mathrm{unintentional}\ \mathrm{in}\mathrm{jury}\ \mathrm{in}\ \mathrm{the}\ \mathrm{prior}\ \mathrm{three}\ \mathrm{months}}{\mathrm{Total}\ \mathrm{number}\ \mathrm{of}\ \mathrm{children}\ \mathrm{that}\ \mathrm{the}\ \mathrm{recruited}\ \mathrm{caregivers}\ \mathrm{look}\ \mathrm{after}}\kern0.5em \times \kern0.5em 100\% $$

Given cultural patterns in China, we anticipate most participants will be caregivers who oversee one single child who meets inclusion criteria, and most families will have just one preschooler when the caregivers are recruited. If an adult caregiver takes care of more than one preschooler, we will enroll only the youngest child when calculating injury incidence. Along with recording injury counts (frequency), we will code external causes of unintentional injury based on the International statistical Classification of Diseases and related health problems 10th revision (ICD-10) [33].

### Secondary outcome measures

We will collect data on several secondary outcomes measures, as detailed below.Caregiver attitudes toward unintentional injury prevention and safety behaviors among preschoolers will be assessed through a 17-item questionnaire. Items will focus on attitudes over the past week; the instrument was validated in previous epidemiological studies and is considered reliable and valid [34, 35]. Two items focus on caregivers’ attitudes for unintentional injury prevention and are assessed using a 4-point scale (completely, partly, not at all, don’t know): (a) Do you think child unintentional injury is largely preventable? and (b) Do you think you can help keep your child free from unintentional injuries? The remaining fifteen items assess caregiver report on the frequency of child’s risky behaviors over the past week, both indoors and outdoors (e.g., leave the child alone in the bathtub; require the child to use a helmet, wrist guard and other protective equipment when riding a bicycle, e-bike, or motorcycle).Caregiver report on economic losses due to unintentional injury will be measured through a 5-item questionnaire that assesses both direct economic costs caused by unintentional injury (medical treatment expenses; transportation expenses to and from hospital/clinic; payment to hire other persons to take care of the injured child; accommodation expenses for the caregivers who look after hospitalized children) and indirect economic costs that are the consequence of unintentional injury events (e.g., caregiver economic loss from being off work).We will also consider the Incremental Cost-Effectiveness Ratios (ICERs) for the app-based unintentional injury intervention. Cost-effectiveness analysis of the app-based unintentional injury intervention will follow National Institute for Health and Clinical Excellence (NICE) guidance on cost-effectiveness evaluation of public health interventions [36]. We will collect data on capital and time costs. Economic costs will consist of subsidies to the researchers and teachers paid by this project, costs for developing and maintaining the app-based interventions, and costs for efforts to increase compliance to using the app-based interventions Caregiver’s time costs will be collected retrospectively for the 6-month follow-up. Because many caregivers may be reluctant or untruthful in reporting their exact wages (individual incomes are regarded as highly private information by many adults in China), we will use the average salary in Changsha, China to calculate the product of total lost months due to taking care of the injured children to estimate the indirect economic loss for adult caregivers because of being off work.

The app-based unintentional injury intervention will be compared to app-based non-injury intervention to assess the incremental costs and benefits of implementing the intervention [37]. The ICERs are calculated as the cost difference between the intervention group and the control group divided by the difference in the number of children experiencing unintentional injury events between the two arms during the prior 6 months (after combining data from the two follow-up surveys). Bootstrap sampling will be used to calculate 95% uncertain interval of the ICERs.

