****Method**:**

A single-blinded, 6-month, parallel-group cluster randomized controlled trial with 1:1 allocation ratio will be conducted in Changsha, China. In total, 2626 caregivers of preschoolers ages 3–6 years old who own a smartphone will be recruited from 20 preschools. Clusters will be randomized at the preschool level and allocated to either the control group (routine education plus app-based parenting education excluding unintentional injury prevention) or the intervention group (routine education plus app-based parenting education including unintentional injury prevention). The app-based injury prevention program was developed based on the Theory of Planned Behavior, the Haddon Matrix, the Mobile Learning framework, and a needs assessment. Data collection will be conducted at baseline, 3-month, and 6-month follow-up via app-based survey plus printed questionnaire survey. The primary outcome measure is unintentional injury incidence among preschoolers in the past 3 months. Secondary outcome measures include economic losses due to unintentional injury in the past 3 months, the Incremental Cost-Effectiveness Ratios (ICERs), and parent’s attitudes and behaviors concerning supervision to prevent preschooler unintentional injury in the past week. An intention-to-treat approach will be used to evaluate outcome measures. Chi-square tests will examine differences for outcome measures between groups at each time point and generalized estimation equations (GEE) will test the overall effectiveness of the app-based intervention. Missing outcome data will be imputed using the Expectation Maximization algorithm (EM).

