### Sample size

Sample size was calculated based on our primary hypothesis, to detect a difference between the intervention and control groups in unintentional injury incidence among preschoolers in the prior 3 months. Previous studies reported an unintentional injury incidence of 25.5% among preschoolers in central China in the past 1 year [22] and an effect size of 0.64 between intervention and control groups [23]. Considering 1 year recall periods underestimate injury rates by 55 and 72% (most are minor injuries) compared with one-month recall periods [24, 25], and use of a strict operational definition that restricts injury events to those that cause activity restriction of 1 day or longer or are treated by a doctor or other medical professional substantially undercounts injury events (typically minor or moderate injuries) [26], we assume unintentional injury incidence among preschoolers in the past 3 months will be 23%. On the basis of a previous report [27], we estimate an intra-class correlation (ICC) of 0.005 within a preschool of 140 students. Predicting an incidence of 23% in the control group, an effect size of 0.75 between intervention and control groups, and an ICC of 0.005, α = 0.05, 1-ß = 0.80, a minimum sample size of 1181 caregivers is needed for each group. Conservatively estimating an attrition rate of 10% in the six-month follow-up study, we will require a recruited sample size of 1323 each group. In total, therefore, we will enroll 2626 participants. Since most preschools have far more than 100 students enrolled, 20 preschools are amply sufficient to recruit the needed sample size.

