### Data collection

Data will be collected at three time points: baseline, 3 months post-intervention, and 6 months post-intervention. All data will be collected through app-based online surveys and will be stored in the backend database of app with password limiting the access. If caregivers fail to complete app-based surveys, we will provide printed paper questionnaires to participants through the support of facilitating teachers. In addition, an independent app-based survey among a sample of 100 caregivers will be conducted at each time period to test the reproducibility of collected data.

We also will collect compliance data through electronic strategies embedded in the app. These will include frequency of login, length of time using the app at each log-in, the number of knowledge disseminations used and listed as bookmarks, the number of published comments, and so on.

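### The ICER cost list leaves out the direct injury costs that the trial itself collects, so averted treatment spending is not netted off

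*Protocol article*

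**What the plan says.** All of this is in the protocol article, mainly under Secondary outcome measures.

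- **Injury costs collected.** A 5-item questionnaire covers "direct economic costs caused by unintentional injury (medical treatment expenses; transportation expenses to and from hospital/clinic", then hired care and accommodation, plus indirect loss from being off work. The Abstract gives the outcome a 3-month window: "economic losses due to unintentional injury in the past 3 months".
- **Costs named for the ICER.** "Economic costs will consist of subsidies to the researchers and teachers paid by this project, costs for developing and maintaining the app-based interventions". The last item in that sentence is spending on measures that encourage people to use the app. Caregiver time comes next: "time costs will be collected retrospectively for the 6-month follow-up". Off-work loss is valued at the average Changsha salary in the same cost-effectiveness text.
- **The ratio.** Its purpose is "to assess the incremental costs and benefits of implementing the intervention". The numerator is described only as the difference in cost between arms. The denominator is the difference in the number of injured children over 6 months, from the two follow-up surveys combined.
- **Data available.** Surveys take place at baseline, 3 and 6 months (Data collection). App use is recorded electronically: "These will include frequency of login, length of time using the app at each log-in".

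**The concern.** The cost-effectiveness text names what goes into the ratio, item by item, and none of the four direct injury costs appears. Yet the trial collects them, and the same text values the indirect loss. A prevented injury would therefore be credited with saved working time but not with saved treatment, transport, hired care or accommodation.

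At stake is how the economic result is read. The Discussion says the economic analyses will demonstrate the app's cost benefit. A ratio that counts spending on the programme but not the direct spending it averts cannot carry that statement. If direct costs per injured child are large relative to programme cost per injured child prevented, it could show a net cost where there is a net saving.

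**Working it through.** The protocol states no ICER, programme cost or unit cost, so there is no figure to reproduce. The check is algebra, with illustrative numbers marked as assumptions.

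**Inputs from the protocol (Sample size):** control incidence 23% per 3 months; ratio 0.75, so 0.23 × 0.75 = 17.25% in the intervention arm; 1181 caregivers per arm before attrition.

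**Notation.** L is the arm difference (intervention minus control) in the costs the text names. I0 and I1 are the numbers of injured children in control and intervention, and D = I0 − I1. c0 and c1 are the mean direct costs per injured child.

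- Ratio as written: L / D
- Ratio with direct costs: (L + c1·I1 − c0·I0) / D
- If c0 = c1 = c, the second equals L / D − c. The ratio as written is then too high by c when D > 0.

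**Amount left out per 1,000 children.** 1,000 × (0.23 − 0.1725) = 57.5 fewer injured children per 3-month period. With c assumed at 100 to 500 yuan: 57.5 × 100 = 5,750 and 57.5 × 500 = 28,750 yuan. Per enrolled child that is 5.75 to 28.75 yuan.

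**When the sign changes.** The ratio with direct costs turns negative once c exceeds L / D. For illustration, treat the two 3-month windows as independent:

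- Control over 6 months: 1 − 0.77² = 0.4071
- Intervention over 6 months: 1 − 0.8275² = 0.3152
- D = 1181 × (0.4071 − 0.3152), which is 108.5 before rounding

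With L assumed at 200,000 yuan, L / D = 1,844 yuan per injured child prevented.

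| Assumed c (yuan) | As written | With direct costs |
|---|---|---|
| 50 | 1,844 | 1,794 |
| 200 | 1,844 | 1,644 |
| 1,000 | 1,844 | 844 |
| 3,000 | 1,844 | −1,156 |

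**When the direction reverses.** The direct-cost term is zero when c1/c0 = I0/I1 = 1/0.75 = 1.33. For one 3-month window, I0 = 1181 × 0.23 = 271.6, I1 = 1181 × 0.1725 = 203.7 and D = 67.9. With L = 200,000 and c0 = 200 (both assumed), the ratio as written is 2,945.

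| c1/c0 | With direct costs |
|---|---|
| 1.0 | 2,745 |
| 1.2 | 2,865 |
| 1.33 | 2,945 |
| 1.5 | 3,045 |

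The ratio as written is therefore too high below 1.33 and too low above it.

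**The case against.** **The list may not be closed.** Caregiver time and off-work loss stand outside the sentence that lists economic costs, so that sentence is not the whole numerator. Off-work loss comes from the same questionnaire as the direct items, which may suggest that injury losses are meant to feed in. The formula speaks only of a cost difference, the analysis is to follow cited NICE guidance that is not at hand, and a fuller document may hold the full cost inventory. It stands that the authors may intend to include direct costs. But the text names items positively and never names these four. If the off-work sentence belongs to the ratio, indirect losses count and direct ones do not. If it belongs only to the separate loss outcome, even less injury cost is in the ratio. Neither reading brings the direct items in.

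**Readers can net the costs off themselves.** Economic losses are a separate secondary outcome compared between arms, and programme cost per injured child prevented is a recognisable measure. This is fair, and is why that version should be kept. It does not give an interval for the net ratio.

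**The size may be small.** Injuries treated only by family first aid count as events (Primary outcome measure), which may pull c down. This stands: importance cannot be shown without unit costs.

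**A stronger reading on caregiver time.** A reader might infer that caregiver time is asked once, with 6-month recall, and is therefore under-reported. The text does not support this. It states no number of collections, and the wording can simply name the period covered. Off-work loss sits in a questionnaire with a 3-month window, with surveys at 3 and 6 months. The recall evidence in Sample size, "Considering 1 year recall periods underestimate injury rates by 55 and 72% (most are minor injuries) compared with one-month recall periods", concerns injury rates over other windows, not time costs. Nor is it stated whether app use or injury care is meant: under-reported app time would lower the ratio, under-reported care time would raise it.

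**Conclusion.** The point holds for the omission of direct injury costs. As written, the ratio does not match its stated aim.

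Its size is c, the mean direct cost per injured child. This rests on two assumptions: the intervention prevents injuries, and c is similar in the two arms. The protocol gives no value for c, so every yuan figure above is illustrative. At the planned 0.75 ratio the error vanishes if each injured child in the intervention arm costs about 1.33 times as much as in control, and it reverses beyond that. A flat statement that the ratio is overstated would therefore go too far, as would a statement that the programme is really cost-saving.

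Only a secondary economic outcome is affected; the primary outcome, randomisation and sample size are untouched. It is still worth correcting, because the direct-cost data are already being collected.

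**What to change.** Define the ICER numerator as the following sum, intervention minus control:

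- programme cost (subsidies, app development and upkeep, compliance efforts);
- caregiver time;
- direct and indirect injury costs from the 5-item questionnaire, summed over the 3- and 6-month surveys.

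Report the programme-cost-only ratio alongside, with the planned bootstrap interval for both. State which caregiver time is meant. Where it is app use, take it from the electronic log. Where it is care of an injured child, make sure it is not counted again as off-work loss. Settle this before costs are seen by arm, so that the choice of numerator cannot depend on the result.

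The cost is wording plus a little more analysis on a secondary outcome. No new survey items are needed for the direct costs.

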### School recruitment

This study plans to recruit participants from 20 preschools in Changsha, China, 10 public and 10 private (note: preschools enroll children ages 3–6 years in China) (Figs. 1 and 2). All schools in Changsha with more than 100 enrolled students will be regarded as eligible schools and will receive an official invitation letter along with related materials about this project. Each facility that agrees to participate will select one teacher to coordinate recruitment of study participants. To avoid unwanted contamination within the same preschool, we will randomly allocate to the intervention versus control group at the school level, stratifying by public/private, such that 10 preschools will be in the intervention group and 10 in the control group, with each group including 5 public preschools and 5 private preschools.

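### The ICER divides by a difference in the number of injured children, so it shifts with arm size, which the design does not fix; costs and effects should be per child

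*Protocol article*

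**What the plan says.** In the Protocol article, Secondary outcome measures, the ICER is "the cost difference between the intervention group and the control group divided by the difference in the number of children experiencing unintentional injury events". The count covers six months, with both follow-up surveys combined. Its uncertainty is covered by one sentence: "Bootstrap sampling will be used to calculate 95% uncertain interval of the ICERs". The resampling unit is not named. The listed costs include "costs for developing and maintaining the app-based interventions", subsidies to researchers and teachers, spending on compliance, and caregivers' time.

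The section Primary outcome measure uses a different scale for the same event: "Our primary outcome variable will be unintentional injury incidence, calculated as" a percentage, with the children cared for by recruited caregivers as its denominator.

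Under School recruitment, "we will randomly allocate to the intervention versus control group at the school level, stratifying by public/private", so that "10 preschools will be in the intervention group and 10 in the control group". On size, "All schools in Changsha with more than 100 enrolled students will be regarded as eligible schools". No upper limit on school size is given, and the article states no rule that holds the number of caregivers equal between arms.

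**The concern.** A difference in counts measures the intervention effect only when both arms contain the same number of children. Here the number of preschools is balanced by design, while the number of children depends on school size and on how many caregivers volunteer at each school. If the intervention arm is larger, it collects more injured children simply because it has more children, and the benefit looks smaller. If it is smaller, the benefit looks larger.

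The cost side does not undo this. Spending that does not grow with enrolment, such as building and maintaining the app, stays the same while the denominator moves. At stake is a named secondary outcome, and the article's Discussion points to cost-effectiveness when it considers wider use of the app.

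**Working it through.** The article states no ICER, cost total or injury count, so there is no figure of its own to reproduce. The check applies its formula to its own planning values.

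**Inputs from the Sample size section:** control risk over 3 months pC = 0.23; effect size 0.75, read as a risk ratio, so pT = 0.75 × 0.23 = 0.1725; total enrolment 2626, or 1313 per arm if equal. (The section also prints 1323 per group, which would double to 2646. The point does not depend on which is meant.)

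**Assumed, not in the article:** the arm splits below; independence of the two 3-month periods for the 6-month risks; the cost figures.

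**Step 1. Split the denominator into its parts.** With nT and nC children per arm and n the average of the two,

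nC·pC − nT·pT = n(pC − pT) − (nT − nC)(pC + pT)/2.

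The first term is the intervention effect. The second is arm size alone. For 1400 intervention and 1226 control: 1313 × 0.0575 − 174 × 0.20125 = 75.5 − 35.0 = 40.5.

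**Step 2. Range of the denominator.** The 6-month risks are 1 − 0.77² = 0.4071 and 1 − 0.8275² = 0.3152.

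| Intervention : control | Fewer injured, 3-month risks | Fewer injured, 6-month risks |
|---|---|---|
| 1313 : 1313 | 75.5 | 120.6 |
| 1400 : 1226 | 40.5 | 57.8 |
| 1226 : 1400 | 110.5 | 183.5 |
| 1444 : 1182 (55:45) | 22.8 | 26.0 |
| 1182 : 1444 | 128.2 | 215.2 |

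The risk difference is the same in every row: 57.5 per 1000 at 3 months and 91.9 per 1000 at 6 months.

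**Step 3. Sign and null case.** The count difference is zero when nT/nC = pC/pT, which is 0.23/0.1725 = 1.33 at the 3-month risks and 0.4071/0.3152 = 1.29 at the 6-month risks. Beyond that, an effective intervention appears to cause injuries. With no effect (23% in both arms), 1400 : 1226 still gives 174 × 0.23 = 40 more injured children in the intervention arm.

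**Step 4. Effect on the ratio.** Assume an extra cost of 100,000 units in the intervention arm that does not depend on enrolment, and the 3-month risks.

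- Count-based ICER: 100,000/75.5 = 1325 with equal arms; 100,000/40.48 = 2470 at 1400 : 1226; 100,000/110.5 = 905 with the split reversed.
- Per-child ICER, (100,000/nT)/0.0575: 1325, 1242 and 1419. This remaining movement only reflects a fixed cost spread over more or fewer children.
- Adding 50 units per caregiver in both arms makes the count-based figures worse: (100,000 + 50 × 174)/40.48 = 2685 and (100,000 − 50 × 174)/110.5 = 826. The per-child figures do not change.

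**Step 5. How likely is imbalance?** If recruited numbers per school have an assumed coefficient of variation CV, the log of the arm-size ratio has standard deviation of about CV × √(2/10). A split of 55:45 or worse in either direction then has probability of about 3%, 14% or 37% for CV of 0.2, 0.3 or 0.5.

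**Step 6. Bootstrap, only if caregivers were the resampling unit.** The planned ICC is 0.005. The design effect 1 + (m − 1) × 0.005 is 1.585 for m = 118 (1181/10) and 1.695 for m = 140 (the stated school size). The true standard error of the risk difference would be √1.585 = 1.26 to √1.695 = 1.30 times the one obtained. In a beta-binomial simulation with ten preschools per arm and mean size 131, coverage of a nominal 95% interval for the risk difference was about 86–88% when individuals were resampled and about 92–93% when preschools were. Average interval widths were 0.061 and 0.073.

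**The case against.** The strongest reply is that the trial aims for 1:1 allocation with ten preschools per arm, five public and five private. With equal arms the count-based and per-child ratios are identical. That is correct, so the harm depends on the imbalance that actually occurs. It does not rescue the formula, because nothing stated in the design makes the arms equal in children.

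A second reply is that the article does not label any cost as fixed, and that some costs, such as compliance incentives and caregiver time, may grow with enrolment. This stands as a limit on the cost illustration. It does not remove the problem, since step 4 shows that a per-caregiver cost shared by both arms adds to the distortion.

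Stronger readings are tempting, but the article does not support them:

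- A reader might infer that the bootstrap ignores the preschools and that its interval is therefore wrong. The article names no resampling unit, and a condensed article may leave this to the full plan. The factor of 1.26 to 1.30 is conditional on resampling caregivers. It also applies to the risk difference and not directly to the ICER interval, which depends on cost variation too.
- A reader might say that the ICER can differ threefold. The figure 110.5/40.5 = 2.7 compares an imbalance with its mirror image. Against the planned equal arms the change is 75.5/40.5 = 1.9-fold or 110.5/75.5 = 1.5-fold.
- A reader might add differential loss to follow-up as a cause of unequal counts. The Data analysis plan specifies intention-to-treat and imputation of missing values, which largely meets this. Unequal enrolment remains.
- A reader might say that national roll-out rests on the ICER. The Discussion only anticipates dissemination if the hypotheses hold, and no decision rule uses the ratio.

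**Conclusion.** The point holds as a defect in a stated formula for a secondary outcome. Taken literally, the denominator depends on arm size, disagrees in scale with the primary outcome, and can shrink, grow or change sign with no change in the true effect. For a modest assumed split of 1400 to 1226, the denominator falls to 40.5 or rises to 110.5, against 75.5 with equal arms (about 58 or 183, against 121, at the 6-month risks). These sizes rest on the assumed split, on reading the effect size as a risk ratio, and, for six months, on independent 3-month periods. With equal arms there is no distortion.

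The bootstrap is not a stated error. The resampling unit should be made explicit, because resampling caregivers would leave the interval moderately too narrow at the planned ICC. The change is worth making, but the trial's primary conclusion does not depend on it.

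**What to change.** Redefine the ICER as the difference in mean cost per enrolled child (intervention minus control) divided by the difference in the 6-month risk of at least one injury (control minus intervention). In the same sentence, state that the bootstrap resamples whole preschools within arm and within public/private stratum.

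No new data are needed, since arm costs, enrolled numbers and both follow-up surveys are already planned. The cost is a little analysis wording and possibly a wider interval than caregiver-level resampling would give.
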